## Abstract

**Background::**

To our knowledge, there have been no published clinical trials to assess the synergistic effects of applying pulsed radiofrequency (PRF) stimulation of the suprascapular nerve (SSN) plus physical therapy on pain and function in patients with adhesive capsulitis. Therefore, we will conduct this present randomized, double-blind study to evaluate the synergistic effects of applying PRF stimulation of the SSN plus physical therapy on pain and function in patients with adhesive capsulitis.

**Methods::**

The study protocol is a randomized, controlled, double-blind design. Recruitment will be started in March 2021 and completed in October 2022. The treating surgeon will assess 90 patients for eligibility. The study protocol was approved through Institutional Review Board in the People's Hospital of Beilun district of Ningbo. Each patient will be randomized into 3 treatment groups, receiving PRF stimulation of the SSN or physical therapy or both of them. After baseline examination, all patients will be given a full explanation of the treatment protocol and will be required to sign a written informed consent for study participation and for publication of the results. All the data collectors, surgeons, statistical analysts, as well as result assessors are not aware of grouping assignment. The outcomes include Constant score, visual analog scale score, range of motion, and strength.

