### Outcomes parameters

2.6

All patients will be assessed for pain and functional status before and immediately after the treatment by a researcher blinded to the patient groups. The range of shoulder mobility and functional status will be assessed using the Constant Shoulder Scale, which was developed to evaluate functional recovery of the shoulder. The total Constant score ranges from 0 to 100 points, with higher scores indicative of better function. The score is divided into four sections: pain (15 points), activities of daily living (20 points), range of motion (40 points), and strength (25 points). Pain is scored using a visual analog scale. The activities of daily living score are divided into 4 subscales of sleep, work, recreational activities, and ability to position the hand in space. Range of motion is assessed in 4 active positions, with 10 points for each. Flexion and abduction are assessed by a goniometer, whereas functional internal and external rotation is assessed by the position of the hand. Strength is tested by a calibrated spring dynamometer, at 90° abduction of the shoulder with the forearm pronated and scored as the maximum of 3 repetitions (Tables 1 and 2).

**Table 1 T1:** Patient baseline demographics.

Demographics	Combined group	PRF lesioning of the SNN group	Ultrasound group	*P*
Number of patients (shoulders)				
Age, yr				
Male sex [no. (%)]				
BMI^∗^, kg/m^2^				
Left side [no. (%)]				
Follow-up^∗^				

BMI = body mass index, PRF = pulsed radiofrequency, SSN = suprascapular nerve.

∗ The values are given as the mean and the SD.

**Table 2 T2:** Postoperative outcomes.

Outcomes	Combined group	PRF lesioning of the SNN group	Ultrasound group	*P*
VAS				
Constant score				
Range of motion				
Muscle strength				

PRF = pulsed radiofrequency, SSN = suprascapular nerve, VAS = visual analog scale. The values are given as the mean and the SD.

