### Statistical analysis

2.7

All analyses will be performed using SPSS for Windows, version 16, and GraphPad InStat. Analysis of variance is used for comparing mean values of patient's age, weight, height, and body mass index. For nonparametric measures such as pain score and functional scores, differences between baseline and posttreatment scores for each group are computed by the Wilcoxon signed ranks test. The difference between each treatment group is performed by the Kruskal--Wallis test. The level of statistical significance is set as *P* < .05. A power analysis is conducted to estimate the requisite sample size. From preliminary research in our hospital, a clinically significant difference reduction in the pain score was defined as 3 cm; a standard deviation of 3.49, probability of a Type I error of 0.05, and power of 0.8 resulted in an estimated sample size of 25. Consequently, a total of 90 subjects will be recruited.

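### No primary outcome is named although the trial is sized on pain alone, and four overlapping outcomes each get an unadjusted test at 0.05

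*Protocol article*

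**What the plan says.** All references are to the protocol article.

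- **Outcomes.** The Methods part of the Abstract gives an unranked list: "The outcomes include Constant score, visual analog scale score, range of motion, and strength". Section 2.6 (Outcomes parameters) does not rank them either. Table 2, headed "Postoperative outcomes", has one row for each of VAS, Constant score, range of motion and muscle strength, with a P column and no row marked as primary.
- **Make-up of the Constant score.** Section 2.6 divides it into "pain (15 points), activities of daily living (20 points), range of motion (40 points), and strength (25 points"), and adds: "Pain is scored using a visual analog scale".
- **Testing.** Section 2.7 (Statistical analysis) says: "The difference between each treatment group is performed by the Kruskal--Wallis test". It then says: "The level of statistical significance is set as *P* < .05". It gives no testing order and no adjustment.
- **Sizing.** The same section bases the calculation on pain only: "a clinically significant difference reduction in the pain score was defined as 3 cm", with a standard deviation of 3.49, type I error 0.05 and power 0.8, giving 25 and a total of 90.
- **Hypothesis.** The Abstract, Introduction and Discussion expect a marked difference in outcomes, in the plural, without saying which outcome decides.

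**The concern.** There are two separate problems.

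First, the sample size takes 0.05 as the type I error for one variable, pain, but nothing ties the trial's conclusion to that variable. Four outcomes are open to a claim at the same level. Anyone who accepts a difference on any one of them as success is working with a false-positive risk above 5%. Only pain has a target difference and a standard deviation; the other three outcomes are not separately sized.

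Second, three of the four Table 2 rows correspond to components of the remaining row. A difference in motion would appear under range of motion and again inside the Constant score, and the two P values could be read as two confirmations of what is largely one effect.

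Which outcome decides the trial is a core protocol choice. The article fixes the outcome list, the results table, the threshold and the sizing variable, and these do not fit together.

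**Working it through.** **1. The plan's own sample size.** Inputs from section 2.7: difference 3 cm, SD 3.49, type I error 0.05 (two-sided assumed), power 0.8. The stated 25 is read as a number per group.

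- Normal approximation: n = 2 × (3.49/3)² × (1.960 + 0.842)² = 2.707 × 7.849 = 21.2, so 22 per group.
- Two-sample t-test: 22.2, so 23.
- Allowing for a rank test (efficiency 0.955): 22.2/0.955 = 23.3, so 24.

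The stated 25 is close to these. The calculation is a two-group comparison of pain and of nothing else.

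**2. The overlap.** From section 2.6: pain 15 + range of motion 40 + strength 25 = 80 of 100 points. The remaining 20 are activities of daily living.

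**3. False-positive risk if any of the four counts.** The independence ceiling is 1 − 0.95⁴ = 18.5%. That ceiling is not attainable if the Constant score is built from the other three.

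A simulation reflects the nesting. It has three groups of 30 (90 split equally, assumed), no true difference, four standardised normal components with a common correlation, and Constant = 15 pain + 20 daily living + 40 motion + 25 strength. Kruskal–Wallis tests at 0.05 are run on pain, Constant, motion and strength, with 40,000 simulated trials per setting. The article gives no correlation, so the range is shown.

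| Component correlation (assumed) | P(at least one of four < 0.05) | Multiple of 5% |
|---|---|---|
| 0 | 16.1% | 3.2 |
| 0.3 | 15.0% | 3.0 |
| 0.5 | 13.5% | 2.7 |
| 0.7 | 11.7% | 2.3 |
| 0.9 | 8.8% | 1.8 |

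A repeat with 60,000 trials per setting agreed to within 0.4 percentage points.

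**4. Power with pain as the single primary.** With 90/3 = 30 per group and no losses: 3/(3.49 × √(2/30)) = 3.329; 3.329 − 1.960 = 1.369; Φ(1.369) = 0.914, about 91% (the t-test also gives 91%). This is for one two-group comparison at 0.05. For a three-group test with means evenly spaced and 3 cm between the extremes, an analysis of variance needs 27.1 per group for 80% power, or 27.1/0.955 = 28.4 for a rank test. Both are below 30.

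**5. The alternative of four co-equal outcomes.** Bonferroni at 0.05/4 = 0.0125 needs 31 to 32 per group for pain. With 30 per group, power falls to about 77%, below the planned 80%.

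**The case against.** The strongest reply is that pain is already the lead outcome in all but name, because it alone has a clinically important difference and a power calculation. A condensed article may also leave testing order and multiplicity to a fuller plan. The second part stands: the absence of a stated adjustment is not by itself the defect. The first part does not settle the matter. Pain is never labelled primary, the Abstract lists the Constant score first, and Table 2 treats all four alike.

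A reader might also infer several stronger things that the article does not support:

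- *That the plan declares success on any of four outcomes.* No success criterion is written. Section 2.7 sets a per-test threshold only, so the any-of-four reading is an inference. Section 2.7 also links the rank tests to pain and functional scores by way of example. Applying Kruskal–Wallis to motion and strength follows from Table 2's P column and is not stated outright.
- *That the error rate is three times 5%.* That multiple fits low to moderate correlation. It falls to about two if the components are strongly correlated.
- *That the overlap causes the inflation.* It does the reverse: shared content lowers the chance of at least one false positive. Double counting is a problem of interpretation.
- *That the other three outcomes are unpowered.* No target difference or SD is given for them, so their power is unknown.

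Finally, the separate VAS and motion rows in Table 2 might come from measurements outside the Constant score. Section 2.6 describes them only within it, so overlap is the natural reading.

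**Conclusion.** The point holds in this limited form. The plan names no primary outcome, sizes on pain alone, and tests four overlapping outcomes at an unadjusted 0.05.

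On the any-of-four reading, the error over the four three-group tests is roughly 9% to 16%, about two to three times the 5% used for sizing. This rests on 30 per group, no true effect, the Constant score modelled as the weighted sum of its parts, and assumed common correlations from 0.9 to 0. It excludes the within-group Wilcoxon tests and any pairwise comparisons. Double counting through the Constant score is a separate matter and does not depend on these assumptions.

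The plan should be corrected, but the fault is one of specification and does not require a different trial.

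**What to change.** Name VAS pain, the variable already used for sizing, as the single primary outcome, tested at 0.05. Define it at one prespecified assessment time that is the same for all three groups. The sponsor must set that time. Section 2.6 says only that patients are assessed before and directly after treatment, and the 12 weeks in section 2.5 are the length of physical therapy, so a common week-12 visit cannot be taken as already planned.

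Make the Constant total secondary, for example tested only if the primary succeeds. Report range of motion and strength as supportive estimates with confidence intervals.

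The cost is mainly protocol wording, plus whatever scheduling the common assessment time requires. No extra patients are needed. The downside is that an isolated difference in motion or strength could no longer be claimed as confirmatory.

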**Results::**

This protocol will provide a reliable theoretical basis for the following research.

**Conclusion::**

It is assumed that there will be a remarkable difference in postoperative outcomes between the intervention and control groups.

**Trial registration number::**

10.17605/OSF.IO/PZ9ES.

## Introduction

1

Adhesive capsulitis, or “frozen shoulder,” is a painful condition commonly encountered in outpatient orthopedic clinics. It has a prevalence of 2% to 5% among outpatients but of about 20% to 30% in patients with diabetes mellitus.^[1]^ The pathogenesis of this condition remains unclear, although associated factors include female sex, trauma, age over 40 years, diabetes mellitus, prolonged immobilization, thyroid disease, stroke, myocardial infarction, and autoimmune disease.^[2]^ Common nonoperative regimens for adhesive capsulitis include supervised neglect with analgesia, supervised physical therapy, an intra-articular corticosteroid injection, a suprascapular nerve (SSN) block, manual brisement, and saline dilatation. No therapeutic intervention is currently universally accepted as most effective for restoring range of motion and decreasing pain in patients with this disease.^[3,4]^

Recent research reported that pulsed radiofrequency (PRF) lesioning of the SSN was effective in treating chronic shoulder pain, including adhesive capsulitis, and it facilitated functional recovery without risking paralysis of the supra- or infraspinatus muscles.^[5]^ PRF is designed to create bursts of heat through the delivery of an electrical field. The short bursts allow for the alleviation of pain in neural tissue, while allowing the tissue to maintain a temperature below 42°C, preventing the nerve damage associated with conventional radiofrequency.^[6]^ Many studies have confirmed the effectiveness of PRF for multiple pain conditions.^[7]^ Recent studies have successfully applied ultrasound-guided PRF stimulation to the medial nerve (carpal tunnel syndrome), interscalene brachial plexus (neoplastic plexopathic pain), intercostal nerve, trigeminal nerve (trigeminal neuralgia), and sciatic nerve (chronic knee pain).^[8–10]^ The ultrasound-guided technique offers improved quality of regional nerve blocks and limits neural trauma. Moreover, ultrasound is radiation-free, more affordable, and more expedient than the computerized tomography and fluoroscopy that are conventionally performed for PRF guidance.

Physical therapy agents including superficial and deep heat with analgesic currents are commonly used to decrease pain and spasm owing to adhesive capsulitis. Rehabilitation methods, including stretching, range of motion, strengthening exercises, and mobilization maneuvers are used to improve joint mobility and restore function. However, these interventions are usually painful and prevent the individual from fully participating in the rehabilitation program. Therefore, PRF lesioning of the SSN may be preferred for adhesive capsulitis before applying physical therapy.^[11,12]^

To our knowledge, there have been no published clinical trial to assess the synergistic effects of applying PRF stimulation of the SSN plus physical therapy on pain and function in patients with adhesive capsulitis. Therefore, we will conduct this present randomized, double-blind study to evaluate the synergistic effects of applying PRF stimulation of the SSN plus physical therapy on pain and function in patients with adhesive capsulitis. It is assumed that there will be a remarkable difference in postoperative outcomes between the intervention and control groups.

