### Recruitment and randomization

2.3

Recruitment will be started in March 2021 and completed in October 2022. The treating surgeon will assess 90 patients for eligibility. Written informed consent will be obtained from patients. Then, each patient will be randomized into 3 treatment groups, receiving PRF stimulation of the SSN or physical therapy or both of them. To allocate treatment, a randomization sequence with random permuted blocks will be generated by randomization program on internet website (www.randomizer.org). Sequentially numbered opaque sealed envelopes containing treatment allocations will be prepared and opened in sequence by an independent research assistant who is not involved in treatment. All the data collectors, surgeons, statistical analysts, as well as result assessors are not aware of grouping assignment (Fig. 1).

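### The aim is synergy, but three arms without a neither-treatment arm support only a claim of added benefit over each component, and the hypothesis and between-group test do not isolate that

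*Protocol article*

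**What the plan says.** The aim appears in the same terms in the Abstract, the Introduction and the Discussion: to "evaluate the synergistic effects of applying PRF stimulation of the SSN plus physical therapy on pain and function".

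Section 2.3 (Recruitment and randomization) gives the arms: "each patient will be randomized into 3 treatment groups, receiving PRF stimulation of the SSN or physical therapy or both of them". The Abstract agrees, and the table shells in section 2.6 also have three columns. No arm receives neither treatment.

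The hypothesis in the Introduction is that "there will be a remarkable difference in postoperative outcomes between the intervention and control groups". It does not say which arm is the control.

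Section 2.7 (Statistical analysis) plans two kinds of test for pain and function. Within arms, "differences between baseline and posttreatment scores for each group are computed by the Wilcoxon signed ranks test". Between arms, "The difference between each treatment group is performed by the Kruskal--Wallis test". The trial is sized on pain: "a clinically significant difference reduction in the pain score was defined as 3 cm", and "a standard deviation of 3.49, probability of a Type I error of 0.05, and power of 0.8 resulted in an estimated sample size of 25". The total is 90. The article does not define synergy, an additivity reference or an interaction contrast.

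**The concern.** In its usual statistical sense, synergy means that two treatments together achieve more than the sum of what each achieves alone. To judge that, one must know what happens under neither treatment, because each single effect is measured from that point. The trial does not observe it.

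The design can show whether the combination is better than PRF alone and better than therapy alone. Both can be true when the two effects simply add up. An investigator whose aim names synergy could then read such a result as confirming it.

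Two further features leave the conclusion loose. The hypothesis contrasts intervention with control without assigning the three active arms to those roles. The only between-arm test named is a three-group omnibus test, which does not say which arms differ.

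**Working it through.** **1. What the sample size was built for.** Inputs from section 2.7: difference 3 cm, SD 3.49, alpha 0.05 (taken as two-sided), power 0.8.

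- Normal approximation, two groups: n = 2 × [3.49 × (1.96 + 0.842) / 3]² = 21.2, so 22 per group.
- Two-sample t-test: 22.2, so 23 per group.
- Rank-test inflation of 22.2: 22.2 / 0.955 = 23.3 and 22.2 / 0.864 = 25.7, so 24 to 26 per group.

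The stated 25 is therefore reproduced as the size per group for a simple two-group comparison. The trial was sized for a pairwise difference, not for an interaction.

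**2. What synergy requires.** Let the improvements in pain be B (both), P (PRF), T (therapy) and U (neither). Synergy on the additive scale is

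S = B − P − T + U.

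The trial observes B, P and T. Suppose they are 6, 3 and 3 cm. Then S = 6 − 3 − 3 + U = U.

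| Assumed untreated improvement U | S |
|---|---|
| −1 cm | −1 cm (less than additive) |
| 0 cm | 0 cm (additive) |
| +1 cm | +1 cm (synergy) |

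The same three-arm data fit all three rows, so the sign of S rests entirely on an assumption. A larger sample does not change this.

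The within-arm comparisons with baseline do not fill the gap. They mix the treatment effect with natural course, regression to the mean and placebo response.

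**3. How often additive effects give a positive trial.** Simulation with normal data, SD 3.49, an assumed 30 per arm (90 / 3) and 10,000 trials per scenario. Improvements are measured beyond natural course, and the combination equals the exact sum of the single effects, so S = 0.

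| Single effects, combined effect | Kruskal-Wallis P < .05 | Combination better than both, each P < .05 (Mann-Whitney) |
|---|---|---|
| 3 and 3, combined 6 cm | about 92% | about 81% |
| 2 and 2, combined 4 cm | about 58% | about 39% |

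The 3 cm effect is the plan's own clinically significant difference. The 2 cm effect is an illustration.

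**4. Whether the omnibus test isolates the combination.** Same settings, with PRF 3 cm, therapy 0 cm and the combination 3 cm, so that the combination adds nothing to PRF alone. Kruskal-Wallis was significant in about 92% of trials. A rule requiring the combination to beat both single arms was met in about 2.6%.

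**5. What estimating synergy would take, for scale only.** With four cells the variance of S is 4 × SD² / n per cell. For an assumed 3 cm interaction, n = 4 × [3.49 × (1.96 + 0.842) / 3]² = 42.5, so 43 per cell and 172 in total. The article gives no interaction size.

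**The case against.** The strongest reply is that the word is used loosely. The article never defines it and claims no interaction. The Introduction and Discussion describe an add-on rationale: PRF relieves pain so that patients can tolerate rehabilitation. At one point the Discussion describes the study simply as investigating PRF plus physical therapy. On that reading three arms suit the question and the fault lies in the wording. This bears on severity. It does not remove the point, because the word stands in every formal statement of the aim and governs what the trial may conclude.

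A reader might infer four stronger things that the document does not support:

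- *Additive benefit will be reported as synergy.* Section 2.7 gives no rule for declaring synergy. It could happen; that it would is a prediction.
- *The trial has no control.* A single-treatment arm is a legitimate active comparator for the combination. The fault is that none is named.
- *Uncertainty about synergy is unlimited.* The Constant score runs from 0 to 100, so the missing mean lies in that range and S is confined to an interval 100 points wide. That is uninformative, but it is not unlimited.
- *Nothing could ever be said about synergy.* If untreated patients are assumed not to worsen (U ≥ 0), a combined improvement larger than the sum of the two single improvements would imply S > 0. The article states no such assumption and plans no such comparison.

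**Conclusion.** The aim is worded more strongly than the design can support. More than additive benefit cannot be estimated from PRF, therapy and both without an untestable assumption about untreated course. A statistical analysis plan that is not shown could not remedy this, since what is missing is a randomised arm.

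The practical exposure is sizeable. With zero synergy and the plan's own 3 cm effects, about 81% of simulated trials showed the combination better than both components, a result open to being called synergy. The single omnibus test adds to the looseness, because it can be significant only because the two single-treatment arms differ from each other.

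These percentages rest on equal allocation, no dropout, normal data and the stated SD. The non-identifiability rests on none of them.

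The design remains sound for the add-on question, so this is a point that should be fixed and not a fatal flaw.

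**What to change.** 1. In the Abstract, Introduction and Discussion, replace the reference to synergistic effects with the added benefit of PRF plus physical therapy over PRF alone and over physical therapy alone.
2. Restate the hypothesis as those two contrasts, with each single-treatment arm as an active comparator, in place of the intervention and control wording.
3. In section 2.7, keep Kruskal-Wallis as the overall test. Name the two pairwise between-group tests and require both to be significant before claiming that the combination is better than each component. Because both must succeed, this claim needs no multiplicity adjustment across the two tests.
4. State that no conclusion on synergy or interaction will be drawn.

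The cost is a more modest claim, a small addition to the analysis, and somewhat lower power than for a single comparison. In the 3 + 3 = 6 cm simulation, the combination beat PRF alone in about 89% of trials and beat both single arms in about 81%. No new arm and no additional patients are needed.
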